## 6.0 Procedures Involved\*

6.1 The randomized controlled design was chosen because it will minimize bias and identify if a causal relationship exists between the use of laser hair depilation and the rate of pilonidal disease recurrence. See Figure 1. Below (note age range 12-21 has changed):

337

**Figure 1**

[figure not shown]

338

339

340

341

342

343

344

345

346

347

348

349

350

351

352

353

354

355

356

6.2 Laser Depilation plus Chemical/Mechanical Depilation group: Subjects randomized to the laser depilation arm will visit the surgery clinic for 1 treatment every 4-6 weeks to obtain a total of 5 treatments. Fitzpatrick skin type classification will be assessed during the initial visit. The Fitzpatrick skin type classification is based on the level of pigmentation of the skin and its response to ultraviolet light (See Appendix). It will be used to select the best laser to perform hair removal for each patient. The laser treatment group will consist of an 810 nm (for Fitzpatrick skin types I-IV) or Nd:YAG (for Fitzpatrick skin types V-VI) 28 joule application at auto pulse duration for 400 ms. A cooling platform and application of 7% lidocaine/ 7% tetracaine cream, applied 45 minutes prior to treatment, will minimize any discomfort associated with the heat of the laser treatments.

The two lasers that will be used in this study (810 nm or Nd:YAG) are both FDA approved for hair removal in all areas of the human body including the back and perineum. Pilonidal disease is not an FDA approved indication for laser hair removal; however, it is being performed commonly in clinical practice. It was determined, by the Director of the

Drug and Device Development Services and the Institutional Review Board (IRB) at NCH that an investigational device exemption is not necessary because we are using an approved device for investigational purposes with non-significant risk. Laser use in this study poses minimal risk to the patient and these minimal risks are similar to the risks associated with hair removal in other regions of the body for which these devices are already FDA approved. Furthermore, our institutional pilot study confirmed the safety and tolerability of these specific laser machines in an adolescent and young adult population.

Similar to the control group, the patients and families in the intervention group will be taught hair removal techniques and asked to perform either chemical or mechanical depilation as needed to keep the area hair-free between clinic treatments. A protocolized “teach-back” method of patient education will be utilized to confirm knowledge of disease process and treatment. The choice between chemical or mechanical depilation between study visits and after completing the 5th study clinic visit is up to the patient and family based on what they are able to do at home. After the 5th visit, the patient and family will be encouraged to continue to perform regular hair removal in the gluteal cleft as needed until the patient reaches age 30. Razors and depilatory the cream will be provided to each subject with instruction on appropriate use during each clinic visit. After the 5th visit, the patients will need to obtain their own supplies.

Standardized scripts and techniques for both the initial and subsequent education and demonstration of hair removal have been developed and will be utilized for both the control and intervention groups. These have been reviewed by patients, families, and physicians and have been tailored for a Flesch-Kincaid reading level between the 5th and 6th grade with presentation of numbers, percentages, and proportions graphically using figures to minimize the effects of differences in numeracy.

#### Control; Chemical/Mechanical Depilation group:

Subjects randomized to the control arm will be provided with the “best recommended standard of care” rather than “usual care” in order to ensure that all control subjects receive uniform information and training on mechanical and chemical hair depilation. Therefore, the control group will undergo an initial visit in which they are educated on the importance and application of chronic hair removal. This initial visit will be reflective of what was felt to be a “best practice” clinic visit in which the treating physician performs education and demonstrates the techniques of mechanical and chemical depilation of the gluteal cleft. In addition, the patient and caregiver will be given supplies for hair removal for the next 6 months. This initial visit will provide a standardized level of education and training about hair removal to all patients in the control group. A protocolized “teach-back” method of patient education will be utilized at this visit to confirm knowledge of disease process and treatment. This

method is routinely practiced within our surgical clinic to facilitate effective communication between staff and patients/caregivers. At each monthly phone follow-up through 4 months, patients in the control group will be encouraged to continue to perform regular hair removal in the gluteal cleft until the patient reaches 30 years of age. The importance of hair removal in preventing disease recurrence and the techniques of hair removal will be briefly reviewed in each of these follow-up sessions. In addition, all patients in the control group will have the option to schedule additional in-person visits for further education and training on hair removal. The choice between chemical or mechanical depilation is up to the patient and family based on what they are able to do at home. The potential effects of the control group having fewer in person visits than the intervention group was discussed within our research team. Consensus was that: 1) having the patients in the control group come for an in-person monthly visit for hair removal and clinical exam was neither pragmatic nor reflective of current clinical practice and completely beyond the best standard of care, and 2) having a similar number of monthly follow-up assessments as the intervention group by phone or email would minimize potential negative effects by allowing for similar data collection and reinforcement of the recommendation for continued hair removal.

### 6.3 Describe:

- Attending surgeons and clinical staff in the surgical clinic will be managing the clinical care of the participants. Vital signs, physical exam and pain scores will be assessed per nursing protocol and surgical service standards. An attending surgeon will assess each patient before and after each treatment. A research team call schedule will be maintained with a member of the study team available by pager 24 hours per day. Any suspected adverse event identified by this person will be discussed with the study PI.
- The laser treatment group will consist of an 810 nm (for Fitzpatrick skin types I-IV) or Nd:YAG (for Fitzpatrick skin types V-VI) 28 joule application at auto pulse duration for 400 ms. A cooling platform and application of 7% lidocaine/ 7% tetracaine cream, applied 45 minutes prior to treatment, will minimize any discomfort associated with the heat of the laser treatments.

The two lasers that will be used in this study (810 nm or Nd:YAG) are both FDA approved for hair removal in all areas of the human body including the back and perineum.

- All baseline and outcome data will be stored electronically in a Research Electronic Data Capture (REDCap) database, which can be accessed only by the appropriate research staff. All

data will be collected in a central REDCap database housed at Nationwide Children's Hospital. To minimize variation and improve the consistency of the interpretation of clinical information, we will utilize standardized data collection forms with established definitions for all variables. See attachment for all surveys/data collected. Although many of our patients return to our institution for subsequent care, some patients may receive care outside of our institution. For patients that receive care outside of our institution, we will capture the events by patient/family report during the follow-up interviews or through medical record review. We will ask for consent from the patient/family and attempt to get the medical records for these encounters to allow us to collect as detailed information about these events as possible.

#### 6.4 Ongoing Assessments

Study staff will conduct data collection at each treatment encounter and at each follow-up time point post- treatment phase. Study staff will contact families with follow-up questions and visit reminders via phone, text, email, and mailed letter, if and when necessary. See attached reminder letter.

In addition, if patients are seen for their pilonidal-related visit at a site outside the NCH network, we will ask participants to sign a release of medical information to obtain visit details regarding the treatment and care they received.

#### Baseline Assessment

Prior to the first treatment, both the patient and legal guardian will be asked to provide demographic and socioeconomic information (SES) including: age, race, ethnicity, gender, annual household income range, patient occupation (from those who work), guardian occupations and specific insurance coverage status. We will also collect a complete medical history of pilonidal disease, family history of pilonidal disease, current pilonidal disease symptoms, current hygiene regime, and history of physician office visits, Emergency Department/urgent care visits and inpatient hospitalizations for pilonidal disease.

The child and legal guardian will be asked to complete the age appropriate PedsQLTM Quality of Life Inventory and questions about healthcare associated disability, pain and pilonidal disease management. The patient will also complete the Child Attitude Toward Illness Scale (CATIS) and the parent and child will complete the disease-related stigma scales. To assist with the costs and time spent participating in the study, parking

484 costs will be paid for by the study and a \$20 research debit card will be  
485 given to the patient or their legal guardian at the end of the visit.

486 **Immediately Following/ 24hrs Post-Treatment (Intervention Group)**

487 Immediately following each laser treatment and 24 hours after, the patient  
488 will be asked to rate their pain from 1-10 utilizing the Numeric Rating  
489 Scale (NRS-11) (see Appendix for Pain Scale). Contact for the 24 hour  
490 follow-up will be completed by phone, text or email.

491 **Follow-up at 1, 2, 3, and 4 months**

492 The patient and legal guardian will complete surveys assessing healthcare  
493 associated disability, pain, pilonidal disease management, and Emergency  
494 Department/ urgent care/ physician office/hospital visits that occurred  
495 between follow-up assessments. In addition, the CATIS will be completed  
496 at the 2 month follow-up, the parent and child disease-related stigma  
497 scales will be completed at the 3 month follow-up, and the age appropriate  
498 Child and Parent PedsQLTM will be administered at the 4 month follow-  
499 up. The Healthcare Satisfaction questionnaire will be administered at the 1  
500 and 4 month follow-ups. These surveys and questionnaires will be  
501 completed at the in-person visits for patients in the laser group and by  
502 either phone or email/web-based survey for patients in the control group  
503 (unless they scheduled an in-person visit for any of these follow-ups, in  
504 which case they will be completed at the in-person visit). To assist with  
505 the costs and time spent participating in the study, a \$20 research debit  
506 card will be given to the patient or their legal guardian at the end of the  
507 visit or mailed to the legal guardian's address (or patient's address if 18  
508 years of age or older) upon successful completion of the surveys.

509 Subjects who will turn 18 before their 1, 2, 3, and 4 month follow-ups will  
510 be asked to sign the informed consent used for the study and to update  
511 their contact information. After speaking with the subject and explaining  
512 the study, an informed consent and contact information sheet will be  
513 mailed to the subjects to sign so that we may continue to collect data up to  
514 24 months after their initial study treatment.

515 **Post-Treatment Follow-Ups at 6, 9, 12, 18, and 24 months**

516 Each subject will receive an email or telephone call at 6, 9, 12, 18, and 24  
517 months after their initial visit. Follow-up will be conducted by email/web-  
518 based survey or by phone with a member of the research team from NCH.  
519 The patient and legal guardian will complete surveys assessing healthcare  
520 associated disability, pain, pilonidal disease management, and Emergency  
521 Department/ urgent care/ physician office/hospital visits that occurred  
522 between follow-up assessments. At 6 and 12 months, the age appropriate

PROTOCOL TITLE: A randomized controlled trial of laser hair depilation in adolescents with pilonidal disease

523 Child and Parent PedsQLTM and the CATIS will be administered. At 9  
524 months, healthcare satisfaction and disease related stigma scales will be  
525 administered. A \$20 research debit card will be mailed to the legal  
526 guardian's address (or patient's address if  $\geq 18$  years of age) upon  
527 successful completion of the surveys at 6 and 9 months. A \$50 research  
528 debit card will be mailed the legal guardian's address (or patient's address  
529 if  $\geq 18$  years of age) upon successful completion of the surveys at 12  
530 months.

531 At the 12 month time point, patients randomized to the control group will  
532 be offered laser treatment, at no cost, contingent on the interim analyses of  
533 adverse events for this study. If these patients choose to receive the  
534 elective laser treatments, they will be brought back into the clinic and re-  
535 consented by the study staff prior to their first treatment. They will have  
536 the option to commit to one or two additional years in the study and will  
537 be followed in the same manner as the patients initially randomized to the  
538 laser intervention group. Data will be collected from the patients per the  
539 same follow-up surveys at 1, 2, 3, and 4 months and post-treatment  
540 follow-up surveys at 6, 9, 12, 18, and 24 months after their initial visit. A  
541 \$20 research debit card will be mailed to the legal guardian's address (or  
542 patient's address if  $\geq 18$  years of age) upon successful completion of the  
543 surveys at 6 and 9 months. A \$50 research debit card will be mailed the  
544 legal guardian's address (or patient's address if  $\geq 18$  years of age) upon  
545 successful completion of the surveys at 12 months. Since laser therapy has  
546 previously been shown to be safe and tolerable, patients and caregivers in  
547 the control group will be informed of the safety monitoring data and the  
548 recurrence rates from the interim analysis when available (Analysis  
549 section above) and allowed to decide if they would like to receive laser  
550 therapy.

551 Subjects who will turn 18 before their 12, 18, or 24 month follow-up will  
552 be asked to sign the informed consent used for the study and to update  
553 their contact information. After speaking with the subject and explaining  
554 the study, an informed consent and contact information sheet will be  
555 mailed to the subjects to sign so that we may continue to collect data up to  
556 24 months after their initial study treatment.

557 **6 months post 1st treatment ( $\pm 30$  days)**

558 A member of the research team from NCH will contact the family over the  
559 phone or email and ask questions about any problems the child has had  
560 with their pilonidal disease since their 30-day follow-up. Specifically, we  
561 will ask about subsequent ED/Urgent Care visits or physician visits,  
562 readmissions and operations, additional imaging, and missed days from  
563 normal activities by the patient and legal guardian that were related to  
564 their pilonidal disease. We will also ask about the out-of-pocket

PROTOCOL TITLE: A randomized controlled trial of laser hair depilation in adolescents with pilonidal disease

565 expenditures directly spent on post-treatment medical care and returning  
566 visits (e.g. insurance copayments; costs of drugs) and other expenditures  
567 related to the visits (e.g. transportation costs) within one year. Please see  
568 the form in the appendix for data points to be collected during this phone  
569 call.

570 For subjects who will turn 18 before their 6-month follow-up, they will be  
571 asked to sign the informed consent used for the study and to update their  
572 contact information. After speaking with the subject and explaining the  
573 study, an informed consent and contact information sheet will be mailed to  
574 the subjects to sign so that we may continue to collect data up to 24  
575 months after their initial study treatment.

576 A \$20 research debit card will be mailed to the legal guardian's address  
577 upon successful completion of the survey.

578 **9 months (±30 days)**

579 A member of the research team from NCH will call or email the family  
580 and ask questions about any problems the child has had with their  
581 pilonidal disease since their six-month follow-up. Specifically, we will ask  
582 about subsequent ED/Urgent Care visits or physician visits, readmissions  
583 and operations, additional imaging, and missed days from normal  
584 activities by the patient and legal guardian that were related to their  
585 pilonidal disease. We will also ask about the out-of-pocket expenditures  
586 directly spent on post-treatment medical care and returning visits (e.g.  
587 insurance copayments; costs of drugs) and other expenditures related to  
588 the visits (e.g. transportation costs) within one year. Please see the form in  
589 the appendix for data points to be collected during this phone call.

590 For subjects who will turn 18 before their 9-month follow-up, they will be  
591 asked to sign the informed consent used for the study and to update their  
592 contact information. After speaking with the subject and explaining the  
593 study, an informed consent and contact information sheet will be mailed to  
594 the subjects to sign so that we may continue to collect data up to 24  
595 months after their initial study treatment.

596 A \$20 research debit card will be mailed to the legal guardian's address  
597 upon successful completion of the survey.

598 **12 months post 1st treatment (±30 days)**

599 A member of the research team from NCH will call or email the family  
600 and ask questions about any problems the child has had with their  
601 pilonidal disease since their 9-month follow-up. Specifically, we will ask  
602 about subsequent ED/Urgent Care visits or physician visits, readmissions

603 and operations, additional imaging, and missed days from normal  
604 activities by the patient and legal guardian that were related to their  
605 pilonidal disease. We will also ask about the out-of-pocket expenditures  
606 directly spent on post-treatment medical care and returning visits (e.g.  
607 insurance copayments; costs of drugs) and other expenditures related to  
608 the visits (e.g. transportation costs) within one year. Please see the form in  
609 the appendix for data points to be collected during this phone call. For  
610 patients that are unresponsive to follow up, we will contact their primary  
611 care physician (PCP) to assess event related to their pilonidal disease.

612 For subjects who will turn 18 before their 12-month follow-up, they will  
613 be asked to sign the informed consent used for the study and to update  
614 their contact information. After speaking with the subject and explaining  
615 the study, an informed consent and contact information sheet will be  
616 mailed to the subjects to sign so that we may continue to collect data up to  
617 24 months after their initial study treatment.

618 A \$50 research debit card card will be mailed to the legal guardian's  
619 address for the completion of this time point.

620 \*If at the 12 month time point, laser depilation is shown to be effective,  
621 patients randomized to the control group will be offered laser treatment at  
622 no cost. Patients choosing to receive laser treatments at no cost will be  
623 also asked to re-consent at this time and will be asked to complete surveys  
624 at the 1, 2, 3, 4, 6, 9, and 12 months follow-up time points. However, only  
625 patients will only receive \$20 for the completion of the 6 and 9month  
626 survey completions, and a \$50 for completion of the surveys at 12 months.  
627 As we are asking this group of standard care to laser care patients to  
628 continue to fill out surveys and attend laser visits (in the same fashion as  
629 the group originally randomized to laser) we will ask these patients to  
630 provide an additional consent at the time that they begin to receive laser  
631 treatments.

632 \* If at the 12 month time point, the subject treated with the laser feel that  
633 they have significant hair re-growth, they will be asked if they would like  
634 to be re-evaluated for further laser hair removal at no cost.

635 **18 and 24 months post 1st treatment (±30 days)**

636 A member of the research team from NCH will call or email the family  
637 and ask questions about any problems the child has had with their  
638 pilonidal disease since their 12 or 24-month follow-up. Specifically, we  
639 will ask about subsequent ED/Urgent Care visits or physician visits,  
640 readmissions and operations, additional imaging, and missed days from  
641 normal activities by the patient and legal guardian that were related to  
642 their pilonidal disease. We will also ask about the out-of-pocket

expenditures directly spent on post-treatment medical care and returning visits (e.g. insurance copayments; costs of drugs) and other expenditures related to the visits (e.g. transportation costs) within one year. Please see the form in the appendix for data points to be collected during this phone call.

For subjects who will turn 18 before their 12 or 24-month follow-up, they will be asked to sign the informed consent used for the study and to update their contact information. After speaking with the subject and explaining the study, an informed consent and contact information sheet will be mailed to the subjects to sign so that we may continue to collect data up to 24 months after their initial study treatment.

Participants will not be reimbursed for the 18 and 24 month follow-up time points.

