## **5.0 Study Intervention/Investigational Agent**

5.1 Subjects randomized to the laser depilation arm will visit the surgery clinic for 1 treatment every 4-6 weeks to obtain a total of 5 treatments. Fitzpatrick skin type classification will be assessed during the initial visit. The Fitzpatrick skin type classification is based on the level of pigmentation of the skin and its response to ultraviolet light (See Appendix). It will be used to select the best laser to perform hair removal for each patient. The laser treatment group will consist of an 810 nm (for Fitzpatrick skin types I-IV) or Nd:YAG (for Fitzpatrick skin types V-VI) 28 joule application at auto pulse duration for 400 ms. A cooling platform and application of 7% lidocaine/ 7% tetracaine cream, applied 45 minutes prior to treatment, will minimize any discomfort associated with the heat of the laser treatments.

The two lasers that will be used in this study (810 nm or Nd:YAG) are both FDA approved for hair removal in all areas of the human body including the back and perineum. Pilonidal disease is not an FDA approved indication for laser hair removal; however, it is being performed commonly in clinical practice. It was determined, by the Director of the Drug and Device Development Services and the Institutional Review

Board (IRB) at NCH that an investigational device exemption is not necessary because we are using an approved device for investigational purposes with non-significant risk. Laser use in this study poses minimal risk to the patient and these minimal risks are similar to the risks associated with hair removal in other regions of the body for which these devices are already FDA approved. Furthermore, our institutional pilot study confirmed the safety and tolerability of these specific laser machines in an adolescent and young adult population.

5.2 Drug/Device Handling: If the research involves drugs or device, describe your plans to store, handle, and administer those drugs or devices so that they will be used only on subjects and be used only by authorized investigators. N/A – We are using a approved device for investigational purposes with non-significant risk.

- If the control of the drugs or devices used in this protocol will be accomplished by following an established, approved organizational SOP (e.g., Research Pharmacy SOP for the Control of Investigational Drugs, etc.), please reference that SOP in this section. – N/A

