## **15.0 Risks to Subjects\***

15.1 Laser Depilation Group Potential risks may include:

- No relief of symptoms
- Recurrence of pilonidal abscess or wound complication
- Photosensitivity or discomfort from laser treatments
- Lastly, loss of confidentiality could be a risk.

Chemical/Mechanical Depilation group:

- Loss of confidentiality could be a risk.

We believe that there is very little risk as a result of being in this study.

Laser treatment may cause some pain or discomfort during and after the laser treatment. We will be applying a topical anesthetic to the skin prior to the laser treatment and will monitor the skin closely for any significant redness or tenderness after the treatment. Trained laser operators will be in the room to make sure the laser is working safely so as to minimize any risks.

The topical anesthetic cream may cause a burning feeling on the skin, a change in color of the skin in that area, or can temporarily affect the way your blood carries oxygen, called methemoglobinemia. We will watch for any of these problems and then check on the area to see if the infection has returned or if it has gotten better as the treatments happen.

971 It is possible that the participant could feel upset when answering  
972 questions about your diagnosis or medical treatment, but it may be more  
973 likely that you find the questions or feedback process a little boring.

974 Although we will take every precaution, there is a small chance of loss of  
975 confidentiality of PHI.

976 15.2 If applicable, indicate which procedures may have risks to the  
977 subjects that are currently unforeseeable.-N/A

978 15.3 If applicable, indicate which procedures may have risks to an  
979 embryo or fetus should the subject be or become pregnant. – N/A

980 15.4 If applicable, describe risks to others who are not subjects. -N/A

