**Sample Study Data Collection Questionnaire: Pilonidal Management**

**(Child):**

The items below will be modified to reflect the appropriate time point in the study

For baseline: wording will be modified to say, in the last month...

For the treatment phase: wording will be modified to say, since you last treatment...

For the follow-up time points: wording will be modified to say, since your last follow-up...

1. In the last month, how many days did you experience pain due to your pilonidal disease?  
\_\_\_\_\_ number of days
2. When you experienced pain, can you tell me how severe the pain was on a scale from 1-10, 1 being no pain and 10 being terrible pain
3. On average, how long would your pain last?
  - a. Minutes
  - b. Hours
  - c. Days
  - d. The entire time, I am still in pain
4. Since your last treatment have you experienced any of the following symptoms?:
  - Swelling, redness, or sore skin in and around the treatment area yes/no  
If yes, did you see a doctor for these symptoms y/n  
If yes, please describe the instructions and treatments that the doctor provided
  - Pus or blood (drainage of pus or blood) in or around the treatment area yes/no  
If yes, did you see a doctor for these symptoms y/n  
If yes, please describe the instructions and treatments that the doctor provided
  - A bad odor coming from the treatment area yes/no  
If yes, did you see a doctor for these symptoms y/n  
If yes, please describe the instructions and treatments that the doctor provided
  - Holes or openings in or around the treatment area yes/no  
If yes, did you see a doctor for these symptoms y/n  
If yes, please describe the instructions and treatments that the doctor provided
5. Since your last treatment did you use nair or shaving for your pilonidal disease?
  - Yes, I used nair only
  - Yes, I used shaving only
  - Yes, I used both nair and shaving
  - No, I did not use either
6. Since your last treatment how often have you used nair (branch from 1 or 3)?
  - More than 1 time per week
  - 1 time per week
  - At least 2 times since the last treatment
  - At least 1 time since the last treatment
  - I did not use the nair at all since my last treatment
7. Did someone help you with applying the nair to the treatment area?
  - Yes
  - No
8. Since your last treatment how often have you shaved (branch from 2 or 3)?

PROTOCOL TITLE: A randomized controlled trial of laser hair depilation in adolescents with pilonidal disease

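### Burns are a stopping-rule event, but the 24-hour contact asks only about pain and no routine clinic visit follows laser session 5, so a late burn can go unrecorded or ungraded

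*Combined protocol and SAP*

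**What the plan says.** **Stopping rule.** Section 4.2 stops the trial if the lower 95% confidence limit for the proportion of laser patients with a study-related SAE exceeds 10%, checked after every 10 patients complete treatment. Only second degree burns and severe pain count. Table 3 gives the thresholds up to 70 patients.

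**Exposure and examination.** Laser patients "will visit the surgery clinic for 1 treatment every 4-6 weeks to obtain a total of 5 treatments" (Section 5.1). Section 6.3 adds: "An attending surgeon will assess each patient before and after each treatment".

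**24 hours.** Under Section 6.4 (Immediately Following/24hrs Post-Treatment), the patient "will be asked to rate their pain from 1-10 utilizing the Numeric Rating" Scale, straight after the session and again at 24 hours. The 24-hour "follow-up will be completed by phone, text or email".

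**After session 5.** "Each subject will receive an email or telephone call at 6, 9, 12, 18, and 24" months (Section 6.4, Post-Treatment Follow-Ups). At month 6 staff use "phone or email and ask questions about any problems the child has had" with pilonidal disease. The only later in-person option is a re-evaluation offered at 12 months for hair regrowth.

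**Skin questions.** The sample questionnaire in the Appendix has "Swelling, redness, or sore skin in and around the treatment area yes/no", followed by whether a doctor was seen and what was done. It is reworded for each time point.

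**Anaesthetic cream.** Section 15.1 lists a burning feeling, colour change and methemoglobinemia, and says "We will watch for any of these problems and then check on the area", without method or timing.

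**The concern.** The two stopping-rule events are not ascertained with equal care. Severe pain is defined over the treatment and the next 24 hours, and a scheduled question covers exactly that window. Burn has no matching prompt. If the skin changes after the patient has left, the plan relies on the next session, on the patient calling or seeking care, or on a later survey.

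Session 5 is the weak point because no next session exists. A burn that has healed by month 6 may be reported only as past redness or soreness, with nothing to grade it by.

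Every miss acts in one direction: it lowers the Table 3 count. That count also reaches beyond stopping. Section 6.4 makes the laser offer to controls at 12 months contingent on the interim adverse event analyses and has control families, many of them with minors, told the safety data. Comparing adverse outcomes is also a secondary objective.

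**Working it through.** **1. Reproducing Table 3.** The thresholds match a two-sided 95% Agresti-Coull interval, taking the smallest count whose lower limit exceeds 0.10:

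ñ = n + z², p̃ = (r + z²/2)/ñ, limits p̃ ± z·√(p̃(1 − p̃)/ñ), with z = 1.96.

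For 3 of 10: ñ = 13.8416, p̃ = 4.9208/13.8416 = 0.3555, half-width 0.2522, limits 0.103 and 0.608, as printed. All seven thresholds (3/10, 5/20, 7/30, 8/40, 10/50, 11/60, 13/70) reproduce. The limits agree within 0.001 (for example 0.110 against a printed 0.111 at 70).

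**2. Timing after session 5.** Four intervals of 4 to 6 weeks put session 5 at 16 to 24 weeks after session 1. Month 6 is about week 26, so the next scheduled skin question comes about 2 to 10 weeks later, or 0 to about 14 weeks with the ±30-day window. After sessions 1 to 4 the next examination is 4 to 6 weeks later. COVID delays lengthened that gap, and delayed patients could complete month 1 to 4 surveys without being seen.

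**3. Effect of missed burns on the rule.** The documents give neither an SAE rate nor a detection share, so these are assumptions:
- 10% of patients have severe pain only, all captured;
- 10% have a burn only, at one session;
- burns are spread evenly over five sessions, and every session-5 burn is missed while the rest are captured.

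True rate = 0.10 + 0.10 = 0.20. Observed rate = 0.10 + 0.10 × 4/5 = 0.18.

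First look, chance of 3 or more in 10:
- at 0.20: 1 − (0.8¹⁰ + 10·0.2·0.8⁹ + 45·0.2²·0.8⁸) = 1 − (0.1074 + 0.2684 + 0.3020) = 0.322;
- at 0.18: 1 − (0.1374 + 0.3017 + 0.2980) = 0.263.

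Carrying the exact binomial distribution of patients not yet stopped through all seven looks gives a chance of stopping by 70 patients of **79.7%** at 0.20 and **67.6%** at 0.18.

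**4. Range.** Share of SAEs detected = 1 − (burn share)/5 when only session-5 burns are lost.

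| True SAE rate | Burn share of SAEs | Observed rate | Stop by 70, all seen | Stop by 70, session-5 burns missed |
|---|---|---|---|---|
| 10% | 50% | 9% | 12.5% | 8.8% |
| 15% | 50% | 13.5% | 44.9% | 33.4% |
| 20% | 25% | 19% | 79.7% | 74.1% |
| 20% | 50% | 18% | 79.7% | 67.6% |
| 20% | 100% | 16% | 79.7% | 52.8% |
| 25% | 50% | 22.5% | 95.8% | 90.1% |

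Table 3 ends at 70. If the same formula were continued to 150 patients (thresholds 14/80, 15/90, 17/100, 18/110, 19/120, 20/130, 22/140, 23/150), the main case would be 96.9% against 90.5%, so part of the loss is delay in stopping.

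**The case against.** Burn capture is not absent. A surgeon re-examines the site before sessions 2 to 5. A study team member can be paged at any hour. The surveys ask about emergency, urgent care, office and hospital visits. The sample questionnaire asks about swollen, red or sore skin and, as reworded for follow-up, the month 6 version reaches back over session 5. The team reviews adverse events as they occur and again each quarter. The questionnaire is only a sample, and Section 6.3 refers to attached forms that are not in the documents. Table 2 lists outcomes, so a missing laser row does not prove that the data go uncollected. The pilot saw no second degree burns in 13 patients.

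Most of this stands, and it limits the point to the 24-hour contact and session 5. It does not remove it: the pager and healthcare-visit routes depend on the patient acting, no item shown names a burn, and grade decides whether an event counts. Thirteen patients cannot exclude a burn rate of 10%.

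A reader might infer two stronger things. One is that missed cream reactions also make the rule under-count. They cannot, because they are not stopping-rule events; missing them is a separate safety-reporting gap. The other is that a large share of burns from all sessions would be lost. Capturing only half of them, for instance, would give an observed rate of 0.15 and a 44.9% chance of stopping by 70. Nothing in the documents supports such a share, and the routes after sessions 1 to 4 speak against assuming it.

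**Conclusion.** The point holds in this form: the 24-hour contact as described has no skin question, and after session 5 burn ascertainment rests on patient-initiated contact, healthcare-visit questions and an ungraded remote survey item. Any resulting miss biases the Table 3 count towards continuing.

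The direction follows from the rule. The size does not follow from the documents. The fall from 79.7% to 67.6% depends on the assumed rates, on even spread over sessions and on loss of every session-5 burn. It shows that the rule is sensitive to missed events; it does not estimate how many would be missed. A burn with severe pain would already be counted through the pain score. If the forms not shown already carry a burn item, the sponsor need only cite it.

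This should be changed because the remedy uses contacts that already take place.

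**What to change.** - Add yes/no items to the existing 24-hour contact: blister, raw skin or burn; skin colour change; and the cream reactions named in Section 15.1.
- Add burn-specific wording to the existing skin item in the month 1 to 4 and month 6 surveys, so that session 5 is covered.
- Send any positive answer to the on-call study team member described in Section 6.3 for review and grading.
- Add a laser adverse event row to Table 2.
- Reconcile Section 4.2, which refers in some sentences to second degree burns and in another to deep ones only, so that it is clear which graded events count. The same section puts the pain threshold both above 8 and at 8 or above; this affects the same count and must be reconciled too.

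The cost is a few questions and a REDCap form change, with no new visit. Contacts become slightly longer, and the recorded SAE count may rise.
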